## **3.6 Criteria for pausing or early termination**

Criteria for pausing:

- Occurrence of one or more  $\geq$  grade 4 adverse reaction or serious adverse event that may be associated with vaccination;
- Occurrence of grade 3 adverse events associated with vaccination in 10% of participants or more.

- Administrative authority call for a complete termination of the trial and explain the reasons.

investigators can terminate the study when any criteria for early termination is met:

- One or more  $\geq$  grade 4 adverse reaction or serious adverse event occur that may probably associated with vaccination;
- Occurrence of grade 3 adverse events associated with vaccination in 15% of participants or more (including injection-site reaction, systemic reaction, and vital signs and abnormal laboratory data);
- The principal investigator call for a complete termination of the trial and explain the reasons;
- Ethics committee call for a complete termination of the trial and explain the reasons;

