| Criteria for pausing or early termination | 
Criteria for pausing:
 
 
- Occurrence of one or more <math>\geq</math> grade 4 adverse reaction or serious adverse event that may be associated with vaccination;
 
- Occurrence of grade 3 adverse events with similar symptoms associated with vaccination in 10% of participants or more.
 
 
Investigators can terminate the study when any criteria for early termination is met:
 
 
- One or more <math>\geq</math> grade 4 adverse reaction or serious adverse event occur that may probably associated with vaccination;
 
- Occurrence of grade 3 adverse events associated with vaccination in 15% of participants or more (including injection-site reaction, systemic reaction, and
 
                                                                                                                                                                                                                                                                                                                                                                                                                                                                         |

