# the evaluation and grading of induration and swelling, rash and redness should be based on the functional level and the actual measurement results, and the indicators with higher classification should be selected.

Table 5 Grading for systemic adverse events.

| Sign                                                           | Grade 1                                | Grade 2                                  | Grade 3                          | Grade 4                            |
|----------------------------------------------------------------|----------------------------------------|------------------------------------------|----------------------------------|------------------------------------|
| Fever [Axillary temperature (°C) ]
>14 years old | 37.3~<38.0                             | 38.0~<38.5                               | 38.5~<39.5                       | ≥ 39.5, last more than 3 days      |
| Gastrointestinal system                                 |                                        |                                          |                                  |                                    |
| Diarrhea                                                       | Mild or transient, 3 to 4 times a day, | Moderate or persistent, 5-7 times a day, | >7 times/day, abnormal stool, or | Hypotension shock, hospitalization |

|                                              |                                                                 |                                                                        |                                                                                                           |                                                                         |
|----------------------------------------------|-----------------------------------------------------------------|------------------------------------------------------------------------|-----------------------------------------------------------------------------------------------------------|-------------------------------------------------------------------------|
|                                              | abnormal stool, or mild diarrhea last less than 1 week          | abnormal stool characteristics, or diarrhea >1 week                    | hemorrhagic diarrhea, orthostatic hypotension, electrolyte imbalance, need intravenous infusion >2L       | required                                                                |

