| Dysphagia                                    | Mild discomfort when swallowing                                 | Diet is restricted                                                     | Diet and conversation are very limited; you can't eat solid food.                                         | Can't eat liquid food; need parenteral nutrition.                       |
| Anorexia                                     | Loss of appetite, but no reduction in food intake               | Loss of appetite, reduced food intake, but no significant weight loss. | Loss of appetite and weight loss                                                                          | Need for intervention (e.g. gastric tube feeding, parenteral nutrition) |
| Vomiting                                     | 1- 2 times/24 hours and does not affect the activity            | 3- 5 times/24 hours or activity is restricted                          | >6 times/24 hours or need intravenous rehydration                                                         | Hypotension shock requires hospitalization or other means of nutrition  |
| Nausea                                       | Transient (<24 hours) or intermittent and food intake is normal | Continued nausea leads to reduced food intake (24-48 hours)            | Persistent nausea results in almost no food intake (> 48 hours) or requires intravenous fluid replacement | Life-threatening (eg hypotension shock)                                 |
| Musculoskeletal and connective tissue |                                                                 |                                                                        |                                                                                                           |                                                                         |
| Non-injection-site muscle pain               | Does not affect daily activities                                | Slightly affect daily activities                                       | Severe muscle pain that seriously affects daily activities                                                | Emergency or hospitalization                                            |

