#### 5.5.4 Relationship between AE and vaccination

Investigators should make the best interpretation of AE, and assess the possible causal relationship between vaccination and reactions (such as history of underlying diseases, combined treatment of causation). This applies to all AEs, including severe ones and non-severe ones. The assessment of causality will be reasonably explained in the following or more aspects of the event: The similar reaction to the solution was observed in the past; identical events of similar types solution have been reported in the literature; the incident occurred along with the time of the vaccination, and again after the secondary vaccination According to definitions, all the solicited AE (that is, the local adverse event of the collection of the report) will be considered to be related to vaccination. The causal relationship of AE should be evaluated according to the following questions, and according to your judgment, the reasonable possibility of relationship between AE and vaccination is caused by the vaccination:

1. Related: there is a suspicion that a link between vaccine and the AE (do not need to be determined);

the vaccine has a reasonable potential for promoting the AE.

2. Unrelated: there is no suspicion that a link exists between vaccine and the AE; there are other more likely causes, and vaccination has not been suspected to promote the AE.

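### The 10% grade 3 pausing rule differs between the protocol abstract and section 3.6, and neither version states its denominator

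*Protocol*

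**What the plan says.** **Grade 3 pause.** The abstract's entry on pausing and early termination reads "Occurrence of grade 3 adverse events with similar symptoms associated with vaccination in 10% of participants or more". Section 3.6 reads "Occurrence of grade 3 adverse events associated with vaccination in 10% of participants or more". Both are current operative text.

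**Grade 3 termination.** Both places allow termination on "Occurrence of grade 3 adverse events associated with vaccination in 15% of participants or more", with no condition on symptom type. Termination is an option open to the investigators, not an automatic consequence.

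**Grade 4 or SAE.** The abstract and section 3.6 agree with each other here. One "grade 4 adverse reaction or serious adverse event that may be associated with vaccination" is enough to pause. Termination becomes available on a grade 4 reaction or "serious adverse event occur that may probably associated with vaccination".

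**Causality.** Section 5.5.4 records two categories. Related means that some link is suspected, without having to be established. Unrelated means that "there is no suspicion that a link exists between vaccine and the AE".

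**Grading.** In Table 5, grade 3 fever ends below 39.5 °C and grade 4 is "≥ 39.5, last more than 3 days". Grade 2 vomiting is 3 to 5 episodes in 24 hours or restricted activity; grade 3 is ">6 times/24 hours or need intravenous rehydration".

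**Denominator.** The rules speak of a percentage of participants. The trial has 60 in each regimen and 120 in all.

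**The concern.** A pausing rule has to give one answer for one set of data. The similar-symptoms condition changes what is counted: the abstract counts participants who share a symptom, while section 3.6 counts participants with any related grade 3 event. Since a participant counted under the abstract is always counted under section 3.6, the section 3.6 rule can be met when the abstract's is not, but never the reverse. Staff working from the abstract could continue dosing when section 3.6 requires a pause.

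The abstract also sits awkwardly with its own termination rule, which has no symptom condition: the 15% termination criterion can be met while the abstract's 10% pause is not.

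The causality scale and the grading table supply the inputs to these rules, so gaps in either leave the decision undefined for some events. A statistical analysis plan could not settle which protocol pausing rule binds the site.

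**Working it through.** **Inputs from the protocol.** Limits of 10% (pause) and 15% (termination) from the abstract and section 3.6; 60 participants per regimen and 120 in total from the abstract and section 3.4. The protocol states no grade 3 rate and no operating characteristic for the rules, so there is no planned figure to reproduce.

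**Step 1: limits as counts.**
- 10%: 0.10 × 60 = 6, or 0.10 × 120 = 12.
- 15%: 0.15 × 60 = 9, or 0.15 × 120 = 18.

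The unstated denominator alone doubles the number of affected participants needed.

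**Step 2: worked cases with 120 participants.**

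| Participants with a related grade 3 event | Largest single-symptom group | Abstract pause | Section 3.6 pause | 15% termination option (both places) |
|---|---|---|---|---|
| 12, as 4 in each of three symptom types | 4/120 = 3.3% | not met | met (10%) | not met |
| 18, as 6 in each of three symptom types | 6/120 = 5% | not met | met (15%) | met |

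**Step 3: how often this could matter.** Assumption, because the protocol gives no rate: four symptoms, independent, each with the same related grade 3 rate q.
- Any grade 3 event: p = 1 − (1 − q)^4.
- Section 3.6 rule: P(Bin(N, p) ≥ 0.10 N).
- Abstract rule: 1 − [1 − P(Bin(N, q) ≥ 0.10 N)]^4.

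| q | p | N | Section 3.6 rule met | Abstract rule met |
|---|---|---|---|---|
| 1% | 3.9% | 60 | 3.1% | about 0 |
| 1% | 3.9% | 120 | 0.3% | about 0 |
| 1.5% | 5.9% | 60 | 13.9% | 0.1% |
| 1.5% | 5.9% | 120 | 5.0% | about 0 |
| 3% | 11.5% | 60 | 69.9% | 3.6% |
| 3% | 11.5% | 120 | 73% | 0.1% |

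For q = 3% and N = 60: p = 1 − 0.97^4 = 0.115; P(Bin(60, 0.115) ≥ 6) = 0.699; P(Bin(60, 0.03) ≥ 6) = 0.009 for one symptom, and 0.036 for at least one of four.

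**Step 4: a second model as a check.** Assume instead that each affected participant has one symptom type, with 2 to 4 equally likely types (200,000 simulated trials). At a true related grade 3 rate of 10%, the two rules disagree in 41% to 55% of trials with N = 60 and 51% to 54% with N = 120. At 5% they disagree in 7% to 8% and 1.7%.

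**Step 5: grade 4 and SAE triggers against section 5.5.4.** An event recorded as Related meets the pause wording. The termination wording asks for a probable association, and section 5.5.4 has no such level. The recorded category therefore cannot show whether the termination criterion is met.

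**Step 6: gaps in Table 5.**
- Fever: 39.5 °C or more for 3 days or less is above grade 3 and does not satisfy grade 4.
- Vomiting: exactly six episodes lies between the counts for grades 2 and 3. Restricted activity would make it grade 2 and intravenous rehydration grade 3, so it is ungraded only when neither is present.

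**The case against.** Only one bullet differs between the two places. The grade 4/SAE triggers and the 15% grade 3 termination option are the same in both, and section 3.6, the full section, carries the more sensitive pause. That limits the damage, but both texts are current and no order of precedence is given.

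A reader might infer that a single grade 4 event or SAE could see the trial continue, pause or stop. The documents do not support that. An event suspected to be associated pauses the trial under either text, and termination is discretionary. Meeting a pause and an optional termination criterion together is ordinary tiering. What stands is that pause and termination cannot be told apart from the recorded category. Graded causality terms do occur in sections 5.5.5 and 8.3.2, but they are not categories of section 5.5.4.

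A reader might also infer that short high fevers drop out of the primary safety results. They do not: that endpoint is the incidence of solicited events within 7 days, whatever their grade. Nor does the SAE trigger depend on grade. An investigator might use the general grading scale after Table 5, but that scale is for events absent from the table, and fever and vomiting are listed. Whether the ungraded values enter the grade-based counts is thus undefined; it does not follow that they are excluded.

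Finally, 70% against 3.6% is one chosen point just above the limit. At low event rates the two rules rarely disagree, so the range must be shown.

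**Conclusion.** The point holds as an internal contradiction in a safety rule. The abstract and section 3.6 state different grade 3 pausing criteria, and neither fixes the denominator. This follows from the text alone, and the case of 18 in 120 shows that the same data give different pausing answers while the termination option is open in both places.

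Its practical size depends on a grade 3 rate that the protocol does not give. Under four independent symptoms with equal rates, the section 3.6 rule is met with probability 0.3% to 3% at 1% per symptom and 70% to 73% at 3%; the abstract rule stays at or below 3.6% throughout.

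Two matters are secondary. The grade 4/SAE pause and termination triggers cannot be separated by the Related/Unrelated scale. Table 5 leaves two narrow sets of values without a grade, which affects the grade-based counts but not the primary incidence endpoint.

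**What to change.** - Reconcile the abstract and section 3.6 into one grade 3 pausing sentence used in both places. It should say whether any related grade 3 event counts or only a shared symptom.
- State the denominator: one regimen or all participants, and whether counting is per dose or cumulative.
- Express the grade 4/SAE pause and termination triggers in categories that section 5.5.4 records, or make section 5.5.4 record the categories that the triggers use.
- Close the fever and vomiting gaps in Table 5 so that every value has a grade.

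Which rule applies and which grades are assigned are decisions for the sponsor's clinical team. The cost is protocol wording, handled as an amendment with ethics committee approval under section 6.2; sample size, visits and analyses are unaffected.

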### **3.7 Duration of study**

It will take about 12 months for each participant from recruiting to completing the last visit.

## **4. Participants**

### **4.1 Participants selection**

Healthy people aged 18 and above who have been vaccinated of a dose recombinant COVID-19 Vaccine (Ad5 Vector), are selected as the target population, and informed in writing by informed consent approved by the ethics committee. On the premise that the volunteers themselves will sign the informed consent, they can only participate in the study after passing the physical examination and the following inclusion and exclusion criteria.

### **4.2 Inclusion criteria**

- The subjects over 18 years old who has completed one dose of recombinant Ad5 vectored COVID-19 vaccine;
- The subjects can provide with informed consent and sign informed consent form (ICF);
- The subjects are able to and willing to comply with the requirements of the clinical trial program and can complete the 6-month follow-up of the study;
- Axillary temperature  $\leq 37.0$  °C.
- Individuals who are in good health condition at the time of entry into the trial as determined by medical history, physical examination and clinical judgment of the investigators and meet the requirements of these products immunization.

### 4.3 Exclusion Criteria

- Have the medical history or family history of convulsion, epilepsy, encephalopathy and psychosis;
- Be allergic to any component of the research vaccines, or used to have a history of hypersensitivity or serious reactions to vaccination;
- Women with positive urine pregnancy test, pregnant or breast-feeding, or have a pregnancy plan within six months;
- Have acute febrile diseases and infectious diseases;
- Have severe chronic diseases or condition in progress cannot be smoothly controlled, such as asthma, diabetes, thyroid disease;
- Congenital or acquired angioedema / neuroedema.
- Have the history of urticaria 1 year before receiving the trial vaccine.
- Have asplenia or functional asplenia.
- Have thrombocytopenia or other coagulation disorders (which may cause contraindications for intramuscular injection);
- Have the history of immunosuppressive therapy, antiallergy therapy, cytotoxic therapy or inhaled corticosteroids (excluding corticosteroid spray therapy for allergic rhinitis, and acute corticosteroid therapy without dermatitis) over the past 6 months;
- Have received blood products within 4 months before injection of trial vaccines;
- Have received another investigational product within 1 month before injection of trial vaccine;
- Have received attenuated vaccine within 1 month before injection of trial vaccine except the recombinant Ad5 vectored COVID-19 vaccine;
- Have received subunit or inactivated vaccine within 14 days before the vaccination with trial vaccine;
- Under anti tuberculosis treatment;
- Not be able to follow the protocol, or not be able to understand the informed consent according to the researcher's judgment, due to various medical, psychological, social or other conditions.

### 4.4 Withdraw from the study

Participants have the right to withdraw from the study at any time during the study period, and the investigators should record the reason of withdraw:

- Loss of contact, early withdraw of the study;

- Request to withdraw without any reason;
- Withdraw for reasons unrelated to the study, such as long-term departure, relocation, etc., and the specific reason for withdrawal should be recorded;
- Withdrawal for reasons related to the study, such as intolerance of adverse reactions, intolerance of biological specimen collection, etc., and the specific reason for withdrawal should be recorded. If a participant withdraw because of AE or SAE, investigators should follow up the participant until the resolve of AE or SAE.
- Participants can require a complete withdraw from the study, all study behaviors can be stopped, including vaccination, biological specimen collection and safety observation. The data before withdrawal will not be used for analysis if he or she require so. If the participants allow the investigators use the data collected before the withdrawal, the data can be included in analysis;
- Participants can require a partially withdraw from the study, such as refuse to vaccination or blood drawn only, but still participate in other procedures during the follow-up.

#### **4.5 Complete of the study**

##### **4.5.1 Complete of the safety data collection**

The participants who receive experimental vaccine, and complete safety observation within 28 days post each booster dose, and reported SAEs through the study will be considered as complete of the safety data collection.

##### **4.5.2 Complete of immunogenicity data collection**

The participants who meet the inclusion and do not meet any exclusion criteria, take the vaccination, and complete the visits and blood collection required by the study protocol will be considered as complete of the immunogenicity data collection.

#### **4.6 Protocol violation and protocol deviation**

##### **4.6.1 Protocol violation (including but not limited to)**

- No informed consent signed by the participant;
- The enrolled participant does not meet the all the inclusion criteria or meet one or more exclusion criteria;
- The participant received incorrect intervention;
- The participant received a vaccine fail to meet the requirements;
- Any other reasons identified by the investigators and confirmed by the principal investigator.

**4.6.2 Protocol deviation (including but not limited to)**

- Beyond the visiting time window;
- Low compliance of participants, and the participants do not complete the blood sample collection;
- Serious adverse events do not report in time (SAE);
- Participants are treated with unallowed drugs (intramuscular, oral or intravenous corticosteroids for  $\geq 2\text{mg/kg/days}$ , continuous use for  $\geq 14$  days, or other immunosuppressants);
- The interval between vaccination with other vaccines is insufficient;
- Other reasons considered as protocol deviation by the principal investigator.

Investigators or monitors should report any protocol violation or deviation to principal investigator or coordinators as soon as possible after knowing it by fax or e-mail. Protocol violation should also be reported to the ethics committees.

**5.0 Methods and procedures****5.1 Participants selection**

Healthy people aged 18 and above who have been vaccinated of a dose recombinant COVID-19 Vaccine (Ad5 Vector), are selected as the target population.

**5.2 Informed Consent**

When obtaining and recording informed consent, researchers should abide by relevant regulations, GCP and the ethical principles stipulated in the Declaration of Helsinki. Before the start of the study, the investigators should obtain written approval/consent from the ethics review committee for the informed consent form and other documents provided to the subjects.

Before participating in this clinical study, researchers should explain the contents of the informed consent form to the subjects and/or their witnesses, and the subjects and/or their witnesses should be given sufficient time to consult the details of the study before signing the informed consent form. When explaining the information of informed consent to multiple persons, each subject and/or witness should be given the opportunity to ask the investigators individually before signing the informed consent form. Researchers should keep the informed consent form signed by each subject, and provide the subject with a copy of the signed name and date of the informed consent form.

